### Adverse events and monitoring safety

All unexpected adverse events related to KRTE and acupuncture treatment will be reported to the investigator or acupuncture practitioner by participants and written on the individual case report form by the investigator. Safety will be assessed by the reporting of clinical laboratory tests, vital sign measurements, and adverse events. Clinical laboratory tests, including AST/ALT, BUN/creatinine, red blood cell (RBC) count, white blood cell (WBC) count, hemoglobin, hematocrit, mean cell volume (MCV), mean cell hemoglobin (MCH), mean cell hemoglobin concentration (MCHC), number of platelets, and number of differentiated cells will be determined at weeks 0 (baseline) and 4 (end of the trial). Vital signs of each participant will be checked with monitoring of adverse events (pain on the acne lesion or other sites, nausea/vomiting, fatigue, allergic reaction, and any adverse events related to KRTE and acupuncture) after each visit.

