#### Baseline data and Outcome data

A two-way analysis of covariance (ANCOVA) test will be used to examine the percentage change of inflammatory and non-inflammatory lesions from baseline to the end of the trial when controlling for baseline and other covariates. A repeated measured ANCOVA test will be performed for evaluation of any significant difference in count of inflammatory and non-inflammatory lesions, Skindex-29 score, and VAS score between baseline and the end of the trial. If there is an interaction between KRTE and acupuncture, only the interaction will be shown. If not, the main effect of KRTE and acupuncture will be reanalyzed and presented. According to 'improvement' or 'no-improvement' of IGA score between baseline and the end of the trial, the difference among the groups will be evaluated using a Chi-square test or Fisher's exact test.

Proportion of drop-outs and compliance with KRTE and questionnaire completion will be calculated and described as n (%). The percentage of subjects in each group will be compared using a Chi-square test or Fisher's exact test.

All adverse events reported during the study will be included in the case report forms; the incidence of adverse events will be calculated. The percentage of subjects with adverse events in each group will be calculated and compared using a Chi-square test or Fisher's exact test.

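### The scope of adverse-event recording is contradictory (unexpected and treatment-related events in one section, all events in another), which risks uneven ascertainment between the waiting list and the treated arms

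*Protocol article*

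**What the plan says.** Two sections of the protocol article define what is recorded as an adverse event.

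- **Adverse events and monitoring safety, spontaneous reports.** "All unexpected adverse events related to KRTE and acupuncture treatment will be reported to the investigator or acupuncture practitioner by participants". The same sentence has the investigator write these events on the individual form. Two conditions apply: the event is unexpected, and it is related to treatment.
- **Same section, monitoring at visits.** "Vital signs of each participant will be checked with monitoring of adverse events", and the scope given is "pain on the acne lesion or other sites, nausea/vomiting, fatigue, allergic reaction, and any adverse events related to KRTE and acupuncture", after each visit. The section also states: "Safety will be assessed by the reporting of clinical laboratory tests, vital sign measurements, and adverse events". Laboratory tests are done at weeks 0 and 4.
- **Baseline data and Outcome data.** "All adverse events reported during the study will be included in the case report forms". Then: "The percentage of subjects with adverse events in each group will be calculated and compared using a Chi-square test", or Fisher's exact test. Neither sentence mentions expectedness or causality.

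Two other facts bear on this. The Waiting list group section gives that arm neither KRTE nor acupuncture for four weeks. The Design section and the Randomization and blinding section blind only the outcome assessor.

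**The concern.** A comparison of adverse-event percentages between randomized arms is informative when the same rule decides, in every arm, whether an event is counted. A rule that counts an event only if it is related to KRTE or acupuncture cannot be applied evenly when one arm receives neither. The same headache or cold might be called related in a treated participant, but cannot be in a waiting-list participant. Participants know their allocation, and they are the first to decide what to report.

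At stake is the between-group safety comparison, not an efficacy outcome. Where the filter operates, background events drop out of the waiting list altogether but only partly out of the treated arms, so the waiting list no longer measures the background rate. One stated aim is to judge the feasibility of a large trial, and safety rates from this pilot may be carried into its planning.

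**Working it through.** The document states no adverse-event rate and no power for this comparison, so there is no figure to reproduce. The check is mainly a comparison of the texts, followed by a bounded illustration.

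**Step 1: which filter applies to which event**

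| Type of event | Spontaneous-report sentence | Visit monitoring | Analysis section |
|---|---|---|---|
| One of the four named symptoms, any cause | only if unexpected and related | yes, no condition | yes |
| Laboratory abnormality | not addressed | tests in the safety assessment at weeks 0 and 4, no condition | yes, if reported as an event |
| Other event, related | only if unexpected | yes (catch-all) | yes |
| Other event, not related | no | no | yes, if reported |

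The last row is the conflict. The analysis section counts such an event if it is reported, but neither intake route in the safety section asks for it. Because the analysis section covers events that are *reported*, it does not by itself widen the intake.

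**Step 2: what this does by arm**

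On the waiting list an event outside the four named symptoms always falls in the last row, because there is no treatment to which it could be related. In the KRTE, acupuncture and combined arms it falls in the third or the fourth row, depending on a causality judgement.

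Let *u* be the percentage of participants whose only event is an unlisted background event, equal in all arms, and *a* the share of these called related. With no true harm:

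- recorded in a treated arm from this source: *u* × *a*
- recorded on the waiting list from this source: *u* × 0 = 0
- spurious difference: *u* × *a*

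With *assumed* values of *u* from 10% to 40% and *a* = 0.5:

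- 10% × 0.5 = 5 percentage points, or 0.05 × 11 = 0.55 participants per arm
- 20% × 0.5 = 10 points, or 0.10 × 11 = 1.1 participants
- 40% × 0.5 = 20 points, or 0.20 × 11 = 2.2 participants

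Named symptoms are recorded in every arm and add nothing to this difference.

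**Step 3: an outer limit that the plan does not reach**

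Suppose no waiting-list event were ever recorded and every event in an active arm were. With 11 per arm (Sample size section), the two-sided Fisher p-value for 0/11 against *x*/11 is 2 × C(11, *x*) / C(22, *x*):

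- *x* = 4: 2 × 330 / 7315 = 0.090
- *x* = 5: 2 × 462 / 26334 = 0.035

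Significance at 0.05 (inferred from the 95% confidence interval, not stated for this test) therefore needs at least 5 of 11. The false-positive rate for the waiting list against one active arm is then P(X ≥ 5), with X binomial (11, *p*). It is compared here with exact enumeration under equal recording:

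| Assumed common rate *p* | Waiting-list events never recorded | Equal recording |
|---|---|---|
| 10% | 0.3% | 0.2% |
| 20% | 5.0% | 1.0% |
| 30% | 21.0% | 1.4% |
| 40% | 46.7% | 1.6% |

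These are pairwise tests, while the plan speaks of comparing the groups. The table shows what a complete filter could do. The named symptoms make the actual filter incomplete.

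**The case against.** The best defence is that the spontaneous-report sentence is not the only intake route. The same section monitors each participant at visits for lesion pain or pain elsewhere, nausea or vomiting, fatigue and allergic reaction. On the natural reading, the relatedness condition attaches only to the final catch-all. No arm is excluded, and laboratory tests and vital signs are added. This stands, and it rules out three stronger readings that a reader might be tempted to infer:

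- *The waiting-list rate is zero by construction.* It is not. A waiting-list participant with fatigue or nausea can be recorded.
- *Expected harms are lost.* The four named symptoms are foreseeable reactions, and they are actively sought. The catch-all also covers other related events without requiring that they be unexpected.
- *The waiting list has fewer monitoring contacts.* It has no treatment sessions, whereas the acupuncture arms have eight. However, the article gives no waiting-list visit schedule, the flow chart is not shown, and VAS and IGA are checked at every session with no arm exempted. Unequal contact is possible but not shown, and a visit calendar may properly sit in the full protocol.

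It can also be said that causality rules and event definitions are detail that an article leaves out. That does not dispose of the point. The article does not omit the rule; it states two that differ. Nor does the monitoring sentence cure it, because its catch-all repeats the relatedness condition, and it does not itself say that its findings go on the form.

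Finally, with 11 per arm a modest distortion amounts to about one participant and will rarely produce a significant test. That is fair, and it limits the consequence for the p-value. It does not make the recorded percentages comparable.

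**Conclusion.** The point holds as an inconsistency of scope with a risk of differential ascertainment. One section seeks unexpected, related events plus a short list of symptoms; the other claims all reported events and tests them across four arms, one of them untreated. For events outside the named symptoms and the laboratory tests, the written rule cannot operate evenly. If followed literally, it would make the treated arms look worse relative to the waiting list, and would understate all-cause incidence in every arm.

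The size cannot be derived from the document. The 5 to 20 percentage points in the illustration rest on assumed background rates, an assumed one-half share called related, and the further assumption that all those background events are unlisted. The false-positive figures up to 46.7% describe a case that the plan does not create. No efficacy outcome is affected. The change is worth making because it is cheap and removes an avoidable bias from the safety comparison.

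**What to change.** Reconcile the safety section with the analysis section so that both use one definition:

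1. Record every adverse event in all four arms, regardless of expectedness or presumed cause, and remove both conditions from the reporting sentence and the catch-all item. State that events found at monitoring go on the case report form.
2. Elicit events in the same way in every arm, with the same question and symptom list, at contacts common to all arms: at minimum baseline and week 4.
3. Have the investigator, not the participant, classify relatedness and expectedness after the event is recorded.
4. Compare all-cause incidence at the common contacts between groups. Describe treatment-related events, and events noted at needling sessions, in the treated arms only and without a test against the waiting list.

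The cost is revised wording, a line on the case report form and longer listings. Reported incidence will be higher, because events that the present wording screens out will be counted.

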### Sample size

This study is a pilot study for evaluation the interaction and efficacy of KRTE and acupuncture in male patients with acne vulgaris and the feasibility of a large clinical trial. Because this trial was designed to be of short duration, lasting four weeks, with the intention of decreasing the drop-out rate, the desired sample size for this pilot study is 44 patients, with 11 for each group, assuming a drop-out rate of 10%.

### Ethics

The study protocol and the written informed consent were approved by the institutional review board (IRB) of the Oriental Medical Hospital at Kyung Hee Medical Center (KOMC IRB 2009-06). Each participant will be notified regarding the study protocol. Written informed consent will be obtained from each patient.

## List of abbreviations

ALT: alanine transaminase; ANOVA: analysis of variance; AO: acupuncture only; AST: aspartate transaminase; BUN: blood urea nitrogen; IGA: investigator global assessment; IRB: institutional review board; KA: KRTE combined with acupuncture treatment; KGMP: Korean good manufacturing practice; KO: KRTE only; KRTE: Keigai-rengyo-to extract; LOCF: last observation carried forward; MCH: mean cell hemoglobin; MCHC: mean cell hemoglobin concentration; MCV: mean cell volume; RBC: red blood cell; RCT: randomized controlled trials; SD: standard WL: waiting list; deviation; TCM: traditional Chinese medicine; VAS: visual analogue scale; WBC: white blood cell.
